#### Exploratory

Absolute change from baseline in maximum Borg score with a minimal clinically important difference (MCID)=1; and Borg score slope during test (measured every minute during CWR).Absolute change from baseline in pedalling time at the same pace and workload.Other statistical analysis of the data collected (questionnaires, test parameters, observations, etc) from participants to investigate the potential effect of neurostimulation (tVNS and TENS) on dyspnoea management.Assessment, through observational notes, of the ease of use and portability of VNS and TENS devices for patients with chronic pulmonary diseases.Assessment of the convenience and practicality of integrating VNS and TENS into their daily routines by patient-reported feedback (by Likert score and by free comments provided).Blinding assessment of the sham will be based on expectation and efficacy questions during visits and the conceptualised sham questionnaire at the end of the last visit.

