Throughout the entire duration of the study, participants’ complete medication regimen will be assessed, and their medication must remain stable during the trial. As part of the pulmonary rehabilitation programme, the eight participants will undergo a medically advised first CPET at VO_2_ max following the data measurement procedures of the study. The Borg scale will be evaluated before the test, every 3 min during the test and at the end of the test. For the baseline visit, only SpO_2_ will be measured before and after CPET. Additionally, spirometry parameters, including FEV1, FVC and FEV1/FVC, will be measured before the test. Data on rehabilitation performance, such as VO_2_ max, breathing and cardiac reserve and the assessment of maximal effort testing, will be useful for the setting of the next two visits. This baseline CWR is crucial as it sets the parameters for the next two experimental visits and as it accounts for the effects of adaptation to the physical test (learning effect), ensuring that any observed changes in subsequent tests are not merely due to physiological adaptations or normal variations that occur in every test conducted under this protocol.

At least 1 week later, at the beginning of this first experimental visit, demographic data and medical records (confirmed via data entry form), the SGRQ and the Psychological Components Questionnaire will be administered. At this point, participants will receive either a cervical or facial neurostimulator, delivering cervical tVNS or trigeminal TENS. Then, they will undergo a submaximal CWR at 80% of VO_2_ max, with the intervention or the sham, and with the same data measurement of the baseline CWR with the addition of more dyspnoea evaluation questionnaires. These include the Borg scale assessed every minute during the test, the mMRC and CAT questionnaires administered before the test, and the VAS recorded before and after CWR. Participants’ expectations regarding the efficacy of the intervention will be assessed at rest, both with and without stimulation. At the end of the protocol, stimulation and perceived efficacy will be evaluated to gather additional subjective data on relief perception and the quality of the sham. Additionally, the time taken to return to the initial Borg score at rest following CWR will be measured. Vital signs, including SpO_2_, HR, BP, RR and T° will also be monitored throughout the entire duration of the test (except BP and T° that are only assessed before CWR).

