Within 2 weeks after the first experimental visit, those who received an intervention (tVNS or trigeminal TENS) will receive the sham, and those who received the sham will receive an intervention. This switch occurs according to the randomisation process of the cross-over group assignment (figure 1). They all undergo a final submaximal CWR, with data collected in the same sequence during the first experimental visit.

In case of technical issues or other concerns affecting the validity of the test or the data collected during one of the visits, an additional visit (W4) could be added after the last experimental visit. If this visit takes place, it will follow the same exercise testing and intervention protocols as the two preceding experimental visits.

If patients experience significant discomfort or adverse effects during the test or interventions, they should immediately inform the healthcare provider so that appropriate measures can be taken to reassure and manage the patient effectively, including possibly stopping the procedure if necessary. The exercise test termination criteria, established by the *American Thoracic Society*, will be followed to ensure participant safety.^56^ Otherwise, common short-term side effects will be assessed frequently, with a minimum of one evaluation at the end of each experimental visit using a standardised questionnaire designed for the interventions of the study. This approach aims to promptly identify and screen for any undesirable effects experienced by participants (online supplemental appendix 10).

Study visits will be completed before starting or before completing the 12-week rehabilitation programme, with a minimal interval to allow recovery after exercise testing while limiting external influences on exercise tolerance assessments. The schedule for data collection of each variable is detailed in online supplemental
table 3*.*

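### Maximum Borg, the only Borg measure given the 1-point threshold, is read at different times under active and sham and is pulled towards no change; add Borg at isotime

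*Protocol article*

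**What the plan says.** All references are to the protocol article.

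- **Outcomes, Exploratory.** The first item is "Absolute change from baseline in maximum Borg score with a minimal clinically important difference (MCID)=1". The same item adds "Borg score slope during test (measured every minute during CWR", with no threshold. The next item is "Absolute change from baseline in pedalling time at the same pace and workload", also with no threshold.
- **Schedule of visits, experimental visits.** Patients receive stimulation and "they will undergo a submaximal CWR at 80% of VO_2_ max, with the intervention or the sham". On dyspnoea measurement the text says "These include the Borg scale assessed every minute during the test". The second experimental visit repeats the same data collection.
- **Schedule of visits, end of test.** "The exercise test termination criteria, established by the *American Thoracic Society*, will be followed to ensure participant safety". No fixed CWR duration is given, and the text does not say outright that the test runs to the limit of tolerance.
- **Schedule of visits, baseline.** "the eight participants will undergo a medically advised first CPET at VO_2_ max", and "The Borg scale will be evaluated before the test, every 3 min during the test and at the end of the test". Later in the same paragraph the baseline test is called a CWR.
- **Statistical analyses.** The Borg slope gets a linear mixed model. Other parameters are compared with and without the intervention by paired t-tests. Borg at a matched time is not mentioned.
- **Sample size and feasibility.** Eight patients, and the study is expressly not designed to determine efficacy.

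**The concern.** Pedalling time can be an outcome only if tests may end at different times, so maximum Borg is not measured at the same exercise duration under active and sham. If stimulation slows the rise of breathlessness, a patient who stops at a personal limit pedals longer and reaches much the same final score. The benefit then appears as time, and the maximum moves little.

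Dyspnoea-limited stopping is plausible here: patients have severe COPD with mMRC grade 3–4 dyspnoea, and the CWR was chosen to provoke the symptom. The 1-point threshold nevertheless sits on the maximum alone. A possible report is a flatter slope, longer pedalling and a clinically important difference not met. That summary would mislead whoever chooses the dyspnoea endpoint of the next trial.

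**Working it through.** **Plan's own figure.** There is none to reproduce. The sample of eight and the threshold of 1 are stated without a calculation.

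**Step 1: baseline cancels between visits.** Let M be maximum Borg at a visit and C the value at baseline. Then (M_active − C) − (M_sham − C) = M_active − M_sham. The paired comparison depends only on the two CWR maxima.

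**Step 2: model (assumed).** Borg rises linearly, Borg(t) = B0 + s·t, and the patient stops at a personal tolerance L. Duration on sham is T = (L − B0)/s. Stimulation cuts the slope by a fraction r. If both tests end at L:

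- change in maximum = L − L = 0
- change at isotime T = −r·(L − B0)
- duration on active = T/(1 − r)

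**Step 3: worked example.** Assumed inputs: B0 = 1, L = 7, T = 6 min, r = 20%. The sham slope is (7 − 1)/6 = 1.0 per min and the active slope is 0.8 per min.

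| Measure | Sham | Active | Difference |
|---|---|---|---|
| Maximum Borg | 7 | 7 | 0 |
| Borg at minute 6 | 1 + 1.0×6 = 7.0 | 1 + 0.8×6 = 5.8 | −1.2 |
| Slope (per min) | 1.0 | 0.8 | −0.2 |
| Pedalling time (min) | 6 | 6/0.8 = 7.5 | +1.5 |

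**Step 4: range.** With B0 = 1, L from 5 to 9, T from 4 to 8 min and r from 10% to 30%, the isotime change runs from −0.10×4 = −0.4 to −0.30×8 = −2.4. The maximum changes by 0 throughout. An isotime change of 1 point needs r = 1/(L − B0): 25% for L = 5, 16.7% for L = 7 and 12.5% for L = 9.

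**Step 5: tests that end for other reasons.** Suppose a share f of patients stop on dyspnoea. The rest stop for another reason at the same time on both days, so their maximum falls by the full 1.2. The mean change in maximum is −1.2·(1 − f).

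| Share dyspnoea-limited | Mean change in maximum | Change at isotime |
|---|---|---|
| 100% | 0.0 | −1.2 |
| 75% | −0.3 | −1.2 |
| 50% | −0.6 | −1.2 |
| 25% | −0.9 | −1.2 |
| 0% | −1.2 | −1.2 |

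The mean maximum reaches 1 point only if f ≤ 1 − 1/1.2 = 0.167.

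**Step 6: noise.** A simulation drew L uniformly from 5 to 9 and T from 4 to 8 min, with about 10% test-to-test variation in slope, rating error of SD 0.5, every test stopping at L, and isotime taken as the last common whole minute. At r = 20% the mean changes were −0.01 for the maximum, −1.05 at isotime, −0.21 per min for the slope and +1.51 min for pedalling time. The SD of the within-patient difference was 0.70 for the maximum and 0.97 at isotime.

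**The case against.** The strongest reply is that the protocol already has the remedy. The slope is in the same item, is fed by minute-by-minute ratings and has its own mixed model. Under a linear rise the isotime difference is only the slope difference multiplied by a fixed time (0.2 × 6 = 1.2), so it carries no new information. Pedalling time would also rise. A reader might therefore infer that the trial would miss real relief, and that inference fails: two of the three exercise measures show it.

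Other stronger readings also go beyond the text:

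- **That maximum Borg is the leading dyspnoea outcome.** The exploratory list sets no hierarchy, and only the slope is named in the analysis section.
- **That the maximum will show exactly no change.** This needs every test to stop at the dyspnoea limit. Stopping at tolerance is inferred from pedalling time being an outcome; the document does not state it.
- **That isotime Borg can replace the outcome as written.** The outcome is a change from baseline, and baseline is described as a maximal CPET rated every 3 minutes. It has no like-for-like value.

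It is also fair to say that the protocol attaches the 1-point threshold only to the maximum, and that its open item on further analyses would permit isotime Borg without any amendment.

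What remains is narrower. The slope is in points per minute, so a threshold in points cannot be applied to it, and pedalling time has no threshold. The protocol's only test of clinical relevance for breathlessness therefore sits on a measure whose timing shifts with treatment. Isotime Borg is the form of the slope information that can be read in Borg points.

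**Conclusion.** The point holds as dilution of one exploratory measure. With test duration free, maximum Borg understates relief in proportion to the share of tests that end at dyspnoea tolerance. In the assumed example with a 1.2-point isotime effect, the mean maximum moves by 0 if all tests are dyspnoea-limited and by −0.6 if half are. It reaches the threshold only if about one test in six or fewer is.

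These sizes rest on a linear Borg rise, a 20% slower rise, a stopping score of 7 and unchanged stopping times in the remaining tests. None of these is in the document.

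The consequence is small: the primary outcome is study completion, there are four patients per device, and the study disclaims efficacy conclusions. The change is worth making because it costs almost nothing and bears on the endpoint a later trial might adopt.

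**What to change.** 1. Add to the exploratory outcomes: Borg at isotime, defined for each patient as the last whole minute reached in both CWR tests, compared active minus sham between visits 2 and 3. Do not express it as change from the baseline CPET. It fits the paired comparison already planned.
2. Judge the 1-point threshold on this difference, and state as an assumption that the threshold carries over from maximum Borg.
3. Keep the slope and its mixed model. Report maximum Borg descriptively beside pedalling time.
4. Reconcile the two labels for the baseline test (CPET and CWR) in Schedule of visits, since both change-from-baseline outcomes depend on which it is.

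**Cost.** Outcome and comparison wording only, with no new visit, measurement or patient burden, because Borg is recorded every minute at both experimental visits. The downside is that ratings after the common minute are not used in the isotime comparison; the slope still uses them. The isotime difference may also vary more between patients than the maximum does (SD 0.97 against 0.70 in the assumed simulation).

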**Methods and analysis:**

We will conduct a feasibility cross-over trial in people with severe COPD and significant exertional dyspnoea referred for pulmonary rehabilitation. Patients will be recruited following the prerehabilitation assessment visit comprising a clinical evaluation and a maximal cardiopulmonary exercise testing on ergocycle. Subsequently, two study visits will be conducted within 2 weeks apart from each other. Eight participants will perform a submaximal constant work rate at 80% workload of the VO_2_ max, either with cervical tVNS (n=4) or trigeminal TENS (n=4). In a cross-over design, both patient groups will undergo sham and active treatment of the neuromodulation technique in a randomly assigned order. The main outcome will be feasibility, assessed by the percentage of patients who attend all visits and complete all tests. Secondary outcomes include other feasibility endpoints, the acceptability and suitability of the interventions (including an evaluation of sham as an exploratory outcome), and the incidence of adverse or undesirable events related to the procedures. Exploratory outcomes include changes in dyspnoea symptoms, measured using standardised questionnaires, such as Borg scale and the Visual Analogue Scale.

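### Two exploratory outcomes and a learning-effect assurance presuppose a baseline constant work rate test, but the only baseline exercise test described is a maximal CPET

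*Protocol article*

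**What the plan says.** **Outcome definitions (Outcomes, Exploratory).** Two items are changes from baseline: "Absolute change from baseline in maximum Borg score with a minimal clinically important difference (MCID)=1" and "Absolute change from baseline in pedalling time at the same pace and workload". The Borg slope is listed beside the first, but is tied to the CWR test itself: "Borg score slope during test (measured every minute during CWR".

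**Baseline test.** The abstract describes a "prerehabilitation assessment visit comprising a clinical evaluation and a maximal cardiopulmonary exercise testing on ergocycle". Schedule of visits says "the eight participants will undergo a medically advised first CPET at VO_2_ max", and earlier in that section the baseline visit is to be checked against published criteria for maximal effort. Borg sampling at this test is also given: "The Borg scale will be evaluated before the test, every 3 min during the test and at the end of the test".

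**The other label for the same test.** Later in the paragraph that introduces the CPET, Schedule of visits says "This baseline CWR is crucial as it sets the parameters for the next two experimental visits". The sentence goes on to credit this test with absorbing the learning effect, so that later changes cannot be put down to adaptation or ordinary test-to-test variation. The next paragraph refers to a baseline CWR again when it sets out the measurements for the experimental visits.

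**CWR tests actually described.** There are two, at visits 2 and 3, both at 80% of VO2 max and both under active or sham stimulation.

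**Planned comparison (Statistical analyses).** Paired t-tests compare parameters with and without the intervention.

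**The concern.** A change in pedalling time at a fixed workload needs a baseline test at that workload. A test taken to maximal effort does not supply one. If the CPET is the baseline, each patient's change combines two things: the move from a maximal test to a constant submaximal load, and whatever stimulation does. Anyone reading the active-condition change by itself could not separate them. Maximum Borg has the same difficulty, and its change is set against a minimal clinically important difference of 1 point.

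The second issue is the assurance about learning. If no CWR test precedes visit 2, patients first meet that test at visit 2, and any familiarisation with it falls between the two visits being compared. The CPET may accustom patients to the ergocycle. It cannot ensure that later differences are free of learning or of normal variation in a different test.

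What is at stake is the meaning of the exploratory signals that are meant to inform a larger trial. An outcome that cannot be obtained as defined could be carried forward into it.

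**Working it through.** **1. The statements side by side.**

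| Place in the protocol article | What it implies about the baseline test |
|---|---|
| Abstract, Methods and analysis | Maximal test on ergocycle |
| Schedule of visits, maximal-effort check | Maximal test |
| Schedule of visits, description of the first test | CPET, Borg every 3 min and at the end |
| Schedule of visits, learning-effect sentence | CWR |
| Schedule of visits, measurements at the first experimental visit | CWR |
| Outcomes, Exploratory, pedalling time | A test at the same workload as visits 2 and 3 |

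The first three rows and the last three cannot describe one test. No unstimulated CWR test is described anywhere in the article.

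**2. What a CPET baseline does to a single condition.** The article gives no loads, ramp rates or test durations, so this is an illustration on assumed values: peak load 40 to 80 W, ramp 5 to 10 W/min, CWR endurance 4 to 8 min, no treatment effect.

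- CPET duration = peak load / ramp: from 40/10 = 4 min to 80/5 = 16 min.
- Change in pedalling time = CWR duration - CPET duration: from 4 - 16 = -12 min to 8 - 4 = +4 min.
- Mid-range case, 60 W peak and 6 min CWR: 6 - 60/5 = -6 min at 5 W/min, and 6 - 60/10 = 0 min at 10 W/min.

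So both the sign and the size of the change can come from the test protocol alone.

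**3. What it does to the crossover contrast.** Write A, S and B for a patient's active, sham and baseline values. Then (A - B) - (S - B) = A - S. The shared baseline drops out, whichever test it was.

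**4. Learning between the two CWR tests.** Let L be the gain from the first CWR test to the second, with no treatment effect. The active-minus-sham difference is +L for a patient who has sham first and -L for one who has active first. The target is four patients per device.

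- Sequences 2:2: mean (2L - 2L)/4 = 0. The SD of the differences due to learning alone is sqrt(4L²/3) = 1.15L.
- Sequences 3:1: mean (3L - L)/4 = 0.5L in absolute value.
- Sequences 2:1, after one loss: mean (2L - L)/3 = 0.33L in absolute value.

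The 1:1:1:1 allocation of eight patients aims at 2:2 within each device. Dropout, or re-randomisation after an exacerbation (which Participants allows), could disturb that.

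**5. Which outcomes are touched.** Pedalling time and change in maximum Borg. The Borg slope is measured within each CWR test and needs no baseline. The difference in Borg sampling, every 3 min against every minute, matters little for the maximum, because Borg is also recorded at the end of the test.

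**The case against.** The strongest reply is that the comparison the article plans is sound. On its natural reading, the paired t-test sets active against sham within patient, and step 3 shows that the baseline cancels there. Sequence is randomised, so learning is balanced in expectation. The article lists learning bias among its limitations and says that the study is not designed to determine efficacy. All of this stands, and it limits the point to outcome definitions and one over-confident sentence.

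A second reply is that baseline could mean the resting value before exercise at the same visit. That could serve for Borg. It cannot serve for pedalling time, which has no resting value.

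Four stronger readings are tempting, and the document does not support them:

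- **That no valid baseline exists.** A reader might infer this, and CPET only is the likelier reading. But the text is contradictory rather than conclusive: it names a baseline CWR twice, and the visit-by-visit schedule is in a supplemental table that is not shown.
- **That protection against learning is absent.** Randomised order protects the active-sham contrast on average, and the CPET gives some familiarisation. Only the stated assurance fails.
- **That every patient would appear to reach the Borg threshold.** This needs a uniform favourable shift of at least 1 point in all eight patients. The article reports no peak Borg values and names no responder analysis.
- **That the flaw is critical to the trial.** No primary or secondary outcome, sample size or error rate depends on these two items.

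**Conclusion.** The inconsistency is real and should be fixed. The article describes a maximal CPET at baseline, while two exploratory outcomes and the learning-effect sentence presuppose an unstimulated CWR test that it does not describe. If the baseline is the CPET, pedalling time cannot be obtained as defined. Changes from baseline in pedalling time and maximum Borg then cannot be interpreted for one condition alone, and the assurance about learning and normal variation is unsupported.

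The reach is narrow: two exploratory outcomes in an eight-patient feasibility trial. The -12 to +4 minute range rests wholly on assumed loads, ramps and durations, and shows only that the artefact could be large in either direction. The cancellation of the baseline and the learning results in terms of L are plain algebra and need no assumed durations.

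**What to change.** 1. Reconcile the abstract, the exploratory outcomes and Schedule of visits, and state which exercise test is done at baseline. If an unstimulated CWR test is in fact performed, describe it.
2. If the baseline is the CPET, define the maximum Borg and pedalling-time outcomes as the within-patient active-minus-sham difference between the two CWR tests. Limit the CPET's role to setting the workload, and correct the two references to a baseline CWR.
3. In that case, replace the learning-effect assurance with a statement that randomised sequence balances learning only on average and that the CPET gives at most partial familiarisation. This would agree with the learning bias already admitted under strengths and limitations.
4. A period term in the analysis is optional. With about four patients per device it would be poorly estimated.

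The cost is wording in the outcome definitions and the visit schedule. No test, visit or patient is added.
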